#### fNIRS data of brain function

2.9.2

fNIRS will quantify task-evoked cortical hemodynamic responses, with Oxy-Hb as the primary hemodynamic indicator because of its sensitivity to task-related changes. These measures will characterize cortical activation and functional connectivity patterns in CID and explore neurofunctional changes after ultrasound-guided SG acupuncture plus conventional acupuncture compared with conventional acupuncture alone.

#### Secondary outcomes

2.9.3

##### PSQI

2.9.3.1

The Pittsburgh Sleep Quality Index (PSQI) is a self-report instrument for the evaluation of sleep quality during the preceding month. The instrument comprises 19 self-rated items, from which seven component scores are generated, each with a score range of 0 to 3. Thereafter, summation of the component scores results in a global score ranging from 0 to 21, with higher scores reflecting poorer sleep quality.

##### HAMA

2.9.3.2

The Hamilton Anxiety Rating Scale (HAMA) is a clinician-rated instrument for the assessment of the severity of anxiety symptomatology. The scale consists of 14 items, each scored on a scale from 0 to 4, thereby yielding a total score ranging from 0 to 56. Total scores are generally categorized as follows: <17, mild anxiety; 18–24, mild-to-moderate anxiety; 25–30, moderate-to-severe anxiety; and ≥31, severe anxiety.

##### Overall clinical efficacy

2.9.3.3

Overall clinical efficacy will be assessed at weeks 4 and 8 as an exploratory categorical outcome adapted from the Guidelines for Clinical Research of New Traditional Chinese Medicine Drugs (2020 Revision). To reduce baseline heterogeneity, sleep-duration improvement will be calculated from each participant’s own baseline value using the raw PSQI sleep-duration item. Outcome categories will be operationally defined as follows:

*Ineffective*: No improvement in sleep disturbance or related symptoms, or the presence of symptom exacerbation.*Effective*: An increase in total sleep time of 1–3 h compared with baseline, with concomitant improvement in related symptoms.*Markedly effective*: An increase in total sleep time of 3–6 h, together with significant improvement in related symptoms.*Cured*: Restoration of sleep duration to a near-normal level (≥6 h), with near-complete resolution of related symptoms.

Accordingly, the overall effective rate will be derived from the proportion of participants categorized as Effective, Markedly effective, or Cured within the total randomized sample, followed by multiplication by 100% for percentage expression.

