#### Eligibility criteria

2.6.2

Participants will be considered eligible for inclusion upon fulfillment of all of the following criteria:

Diagnosis of CID in accordance with the ICSD-3 diagnostic criteria, together with an ISI score of ≥10.Age between 18 and 70 years, with no sex-based restriction, and right-handedness.No use of medications or other therapeutic interventions for insomnia within 1 month prior to enrollment.Preserved ability for normal communication and compliance with study procedures.Written informed consent must be provided.

Healthy controls will be required to meet all of the following criteria:

Right-handed individuals of either sex, aged between 18 and 70 years;An ISI score ≤7, a Pittsburgh Sleep Quality Index (PSQI) score ≤5, and a HAMA score <7;No history of major chronic diseases or severe organic dysfunctions (e.g., cardiovascular, hepatic, or renal diseases);No use of hypnotics, antidepressants, central nervous system stimulants, or any other medications/substances known to substantially affect sleep architecture or central nervous system function within 1 month prior to enrollment;Voluntary provision of written informed consent prior to study participation.

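### The overall clinical efficacy categories are neither exhaustive nor mutually exclusive, and the sleep part of Cured can be met with no gain from baseline

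*Protocol article*

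**What the plan says.** The protocol article, section 2.9.3.3, presents the four categories as operational definitions:

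- Ineffective: "No improvement in sleep disturbance or related symptoms, or the presence of symptom exacerbation".
- Effective: "An increase in total sleep time of 1–3 h compared with baseline, with concomitant improvement in related symptoms".
- Markedly effective: "An increase in total sleep time of 3–6 h, together with significant improvement in related symptoms".
- Cured: "Restoration of sleep duration to a near-normal level (≥6 h), with near-complete resolution of related symptoms".

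On measurement it says that "sleep-duration improvement will be calculated from each participant’s own baseline value using the raw PSQI sleep-duration item". The summary statistic is the "proportion of participants categorized as Effective, Markedly effective, or Cured within the total randomized sample".

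On status, the Abstract, Table 1 and section 2.9.3 list the outcome as secondary, while section 2.9.3.3 itself says "Overall clinical efficacy will be assessed at weeks 4 and 8 as an exploratory categorical outcome".

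Section 2.6.2 admits patients who have an ICSD-3 diagnosis "together with an ISI score of ≥10". Neither that section nor the diagnostic and exclusion criteria (2.6.1 and 2.6.3) put an upper limit on baseline sleep duration.

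**The concern.** A categorical outcome can be analysed only if each patient falls into exactly one category. Here two categories are bounded by gain from baseline, one by absolute duration, and one by an absence of improvement with no numeric bound. These bounds do not meet. No order of precedence is given, and the symptom terms (improvement, significant improvement, near-complete resolution) have no threshold.

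An assessor who meets a patient outside all four categories must either leave the patient unclassified or choose a category by judgement. An unclassified patient stays in the all-randomized denominator and so counts as non-effective by default. A patient who meets both Ineffective and Cured can be counted as a success or a failure. Blinded assessment limits bias in such choices but does not say which category applies.

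Sections 2.6.1 and 2.6.2 also allow a patient with, say, 6.5 h of sleep and an ISI of 10 or more to enter. That patient satisfies the duration part of Cured on day one.

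**Working it through.** The article gives no numerical result for this outcome, so there is no figure to reproduce. The check is to apply the four definitions to patient profiles.

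**Inputs.** Bounds from section 2.9.3.3: Effective, gain 1–3 h; Markedly effective, gain 3–6 h; Cured, final sleep of 6 h or more. Final sleep = baseline + gain. Symptom levels are ordered worse, unchanged, improved, significantly improved, nearly resolved, and a higher level is taken to satisfy a lower requirement. For Ineffective, sleep disturbance is judged by the sleep gain, and the word joining the two conditions is read in two ways:

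- Reading A: neither sleep nor symptoms improve, or symptoms worsen.
- Reading B: at least one of the two fails to improve, or symptoms worsen.

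| Baseline to final sleep | Gain | Symptoms | Reading A | Reading B |
|---|---|---|---|---|
| 5 to 5.5 h | 0.5 h | improved or significantly improved | none | none |
| 4 to 4.5 h | 0.5 h | nearly resolved | none | none |
| 6.5 to 7 h | 0.5 h | significantly improved | none | none |
| 2.5 to 6 h | 3.5 h | improved, not significantly | none | none |
| 5 to 7 h | 2 h | unchanged | none | Ineffective |
| 5 to 5 h | 0 h | improved | none | Ineffective |
| 2.5 to 5.5 h | 3 h | significantly improved | Effective and Markedly effective | same |
| 5 to 7 h | 2 h | nearly resolved | Effective and Cured | same |
| 3 to 7 h | 4 h | nearly resolved | Markedly effective and Cured | same |
| 6.5 to 6.5 h | 0 h | nearly resolved | Cured | Ineffective and Cured |

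**Gaps.** Rows 1 to 4 have no category on either reading. Rows 5 and 6 have none on reading A only.

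**Overlaps.** Rows 7 to 9 have two categories on either reading. Row 10 has two on reading B only.

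**Effect on the overall effective rate.** Rate = (Effective + Markedly effective + Cured) / all randomized.

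- Rows 7 to 9: both candidate categories are in the numerator, so the rate does not change; only the category counts do.
- Rows 1 to 6: on the printed formula an unclassified patient is outside the numerator and counts as non-effective. If the patient is instead placed by judgement, the rate can move.
- Row 10: the rate depends on which of the two categories is chosen.

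With 40 randomized per group (section 2.3), each patient reassigned in this way moves a group's rate by 1/40 = 2.5 percentage points.

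**The case against.** The strongest reply has five parts.

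- **Status.** The outcome is described as exploratory, and no primary endpoint, alpha allocation or sample size rests on it. This stands and limits the weight of the point.
- **Overlaps.** A reader might infer that the overlaps inflate the effective rate. The formula does not support that: overlaps among Effective, Markedly effective and Cured leave it unchanged.
- **Gain of 1 h or more without better symptoms.** A reader might infer that this patient certainly has no category. That depends on the reading of Ineffective: on reading B the patient is Ineffective. What stands is that the text does not settle which reading applies.
- **Long sleepers.** A reader might infer that they are counted as cured without any change. They are not: Cured also requires near-complete symptom resolution, and the notion of restoration hints at a shortfall at baseline. An absolute threshold is also defensible for a remission category. What stands is that no rule requires a shortfall or a gain, so the duration part can be met unchanged.
- **The main gap and the rate.** Making gains under 1 h Ineffective gives the same rate as leaving them unclassified in the denominator. That is correct; the benefit is that judgement is removed and the category counts add up.

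It might also be said that such detail belongs in a statistical analysis plan. But the article prints the complete rule, with numerator and denominator, and the defect lies in what it prints.

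**Conclusion.** The point holds on the text. The four categories do not cover all patients, they overlap without a precedence rule, and the duration part of Cured requires no gain although baseline sleep has no ceiling at entry. The overall effective rate is exposed through the gaps and, on reading B, through the Ineffective/Cured overlap. The remaining overlaps affect category counts only. The primary ISI and fNIRS analyses are untouched, so this should be corrected but does not threaten the trial's main conclusions.

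A reader might infer that a large fraction of patients would be unclassifiable. The documents do not support any such figure, because they give no distribution of baseline sleep or of sleep gain. An illustration with wholly assumed inputs (baseline mean 4.5–5.5 h, SD 1.2 h; gain mean 0.5–1.5 h, SD 1 h; assumed symptom cut-points correlated with gain) leaves about 28–42% unclassified on reading A and 6–14% on reading B. That spread shows how far the answer depends on the reading and the assumptions; it is not an estimate for this trial.

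The profile classification rests on judging sleep disturbance by sleep duration. If symptom relief alone counted as improved sleep disturbance, row 10 would be Cured only.

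**What to change.** Before unblinding, restate the rule so that it is applied top-down and each patient stops at the first category met:

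1. Cured.
2. Markedly effective.
3. Effective: any gain of 1 h or more with symptom improvement that does not meet a higher category.
4. Ineffective: everyone else, which removes the ambiguity between readings A and B.

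Assign a gain of exactly 3 h to one category. Do not cap Effective below 3 h, since a cap would turn a 4 h gain with lesser symptom improvement into Ineffective.

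State how patients with baseline sleep of 6 h or more are handled, for example by requiring a gain from baseline for the sleep part of Cured. The size of that gain is the sponsor's choice and should be tested on borderline profiles: a 1 h minimum would make a patient going from 5.5 h to 6 h with full resolution Ineffective.

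Tie the symptom terms to a scale already collected, such as the ISI, accepting that the outcome then partly repeats a primary endpoint.

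The cost is a rewritten definition, with the ethics approval and the registry and analysis plan updates that section 2.12 requires for a change to outcomes. No new data are needed. The downside is that some category counts, or the effective rate, may look less favourable.

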### Assessment of safety

2.10

All adverse events (AEs) during intervention and follow-up will be recorded, including onset, duration, severity, management, outcome, and causality. AEs will be graded as mild, moderate, or severe. Mild AEs include transient symptoms requiring no specific treatment, such as local pain, minor ecchymosis, or transient dizziness. Moderate AEs include symptoms requiring clinical management or observation, such as persistent local pain, moderate hematoma, vasovagal reaction, transient hoarseness, dysphagia, or ipsilateral ocular symptoms. Severe AEs include marked functional impairment, hospitalization, or serious events such as suspected neurovascular injury, airway compromise, severe dyspnea, expanding cervical hematoma, pneumothorax, or loss of consciousness.

Common needle-related AEs, including minor bleeding and localized pain, will be managed according to standard clinical protocols. In cases of dizziness or needle syncope, the procedure will be immediately terminated; the participant will be placed in a supine position with continuous monitoring of vital signs and oxygen saturation (SpO2) until complete recovery. Supportive care will be provided as necessary, and participants with persistent symptoms will be referred to the emergency department for further evaluation. Specific attention will be given to AEs related to ultrasound-guided SG acupuncture, such as hoarseness, dysphagia, dyspnea, choking sensations, radiating paresthesia, and symptoms suggesting recurrent laryngeal nerve, phrenic nerve, vascular, or pleural involvement. Upon occurrence of these symptoms, needle manipulation will cease immediately, and the needle will be withdrawn under ultrasound guidance. Vital signs, airway patency, and neurological functions will be assessed immediately, with oxygen therapy administered if indicated. Participants exhibiting persistent complications (e.g., progressive neck swelling, suspected pneumothorax, or unstable vital signs) will be transferred to the emergency department and referred to appropriate specialists, including anesthesiology, otolaryngology, or vascular surgery.

Vital signs will be measured before and after each treatment, and participants receiving SG acupuncture will be observed for at least 30 min. Serious AEs will be reported to the ethics committee within 24 h. Participants who discontinue or suspend components for safety reasons will continue to receive appropriate medical evaluation and will be encouraged to complete outcome follow-up whenever ethically and clinically appropriate.

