**Figure 1 fig1:**
[figure not shown]
The flowchart of trial procedures.

**Table 1 tab1:** Schedule of enrolment, interventions and outcome assessments.

Timepoint	Baseline		Treatment phase	Follow-up phase
	Week −1	Week 0	Week 1–4	Week 8
Participants				
Eligibility screen	×			
Signed informed consent		×		
Clinical interview		×		
Physical examination		×		
Randomization		×		
Interventions				
treatment group		×	×	
Control group		×	×	
Primary outcomes				
ISI		×	×	×
fNIRS assessment		×	×	×
Secondary outcomes				
PSQI		×	×	×
HAMA		×	×	×
Overall clinical efficacy			×	×
Assessments				
Adverse events		×	×	
Use of sleep medications		×	×	×
Patients’ compliance		×	×	×

ISI, the insomnia severity index; PSQI, Pittsburgh sleep quality index; HAMA, Hamilton anxiety scale. × = Implementation of the corresponding project at the corresponding point in time.

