### Recruitment and procedure

2.5

Recruitment will take place at Tongde Hospital of Zhejiang Province Affiliated to Zhejiang Chinese Medical University through outpatient clinics and online notices distributed via WeChat. Recruitment materials will describe the target population, eligibility criteria, intervention procedures, and contact details. Interested individuals will receive a study brochure and complete a screening form. Eligible patients with CID will then undergo baseline assessment and randomization. Outcome assessments will be conducted at baseline, week 4 (post-treatment), and week 8 (follow-up). Healthy controls will be recruited as a reference group for baseline fNIRS comparison only. Before fNIRS assessment, their eligibility will be verified through clinical interview and baseline assessments.

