### Intervention

2.8

Licensed acupuncturists with at least 5 years of clinical experience will receive standardized training before trial initiation. Both groups will receive the same conventional acupuncture prescription: Sishencong (EX-HN1), Anmian (EX-HN22, bilateral), Shenmen (HT7, bilateral), Sanyinjiao (SP6, bilateral), Shenmai (BL62, bilateral), and Zhaohai (KI6, bilateral). Detailed acupoint locations are shown in Table 2 and Figure 2. Treatment will include 12 sessions over 4 weeks, three sessions per week. In the treatment group, ultrasound-guided SG acupuncture will be performed first, followed immediately by conventional acupuncture; after all needles have been inserted, needles will be retained concurrently for 30 min.

**Table 2 tab2:** Locations of selected acupoints.

Acupoint	Location
Sishencong (EX-HN1)	Located on the head, at four points situated 1 cun anterior, posterior, and lateral to Baihui (GV20).
Anmian (EX-HN22)	At the halfway point between Fengchi (GB20) and Yifeng (SJ17)
Shenmen (HT7)	Located on the anterior wrist region, at the ulnar end of the transverse crease of the palm, on the radial side of the tendon of the flexor carpi ulnaris.
Shenmai (BL62)	Located in the ankle region, directly inferior to the prominence of the lateral malleolus, in the depression between the lower border of the lateral malleolus and the calcaneus.
Zhaohai (KI6)	Located in the ankle region, inferior to the prominence of the medial malleolus, in the depression along the lower border of the medial malleolus.
Sanyinjiao (SP6)	Located on the medial aspect of the lower leg, 3 cun superior to the prominence of the medial malleolus, posterior to the medial border of the tibia.

cun: proportional bone (skeletal) cun. Baihui (GV20): located on the head, 5 cun directly superior to the midpoint of the anterior hairline. Fengchi (GB20): located in the posterior cervical region, inferior to the occipital bone, in the depression between the upper portion of the sternocleidomastoid muscle and the upper portion of the trapezius muscle. Yifeng (SJ17): located in the neck region, posterior to the earlobe, in the depression anterior to the inferior aspect of the mastoid process.

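### Table 1 schedules no adverse-event enquiry at week 8, although section 2.10 commits to recording adverse events through follow-up

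*Protocol article*

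**What the plan says.** Section 2.10 (Assessment of safety) sets the collection window: "All adverse events (AEs) during intervention and follow-up will be recorded". For each event it also asks for timing, duration, grade, handling, outcome and causal attribution.

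Section 2.5 (Recruitment and procedure) places the visits: "Outcome assessments will be conducted at baseline, week 4 (post-treatment), and week 8 (follow-up". Section 2.8 (Intervention) fixes the treatment period: "Treatment will include 12 sessions over 4 weeks, three sessions per week". Follow-up is therefore the interval from week 4 to week 8, and the Discussion confirms that week 8 is the last assessment.

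Section 2.2 refers the reader to Table 1 for the assessment schedule. Its time columns are "Week −1 Week 0 Week 1–4 Week 8", and its legend defines a mark as "Implementation of the corresponding project at the corresponding point in time". The row "Adverse events" is marked under Week 0 and Week 1–4, and its Week 8 cell is empty. The other two rows of that block, "Use of sleep medications" and "Patients’ compliance", are marked under Week 0, Week 1–4 and Week 8.

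**The concern.** The safety section and the schedule describe different collection windows, and both are current text. Site staff who work from the schedule would have no prompt to ask about adverse events at the final visit.

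Three features of this trial make that more than a drafting matter.

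- Section 2.10 requires the duration and outcome of each event. For an event still open at week 4, these can be completed only at a later contact, and week 8 is the only one scheduled.
- The severity grading depends partly on whether a symptom is transient or persistent, which also needs later observation.
- Only the treatment arm receives bilateral ultrasound-guided needling near the stellate ganglion. The Discussion acknowledges that there is no sham, so patients can tell whether they had the neck procedure. Without a common question, a patient's readiness to volunteer a symptom in weeks 5–8 may differ by arm, and so may the investigators' readiness to note it.

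The Introduction presents the technique as potentially safer than stellate ganglion block, so even-handed safety data bear directly on the trial's rationale.

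**Working it through.** There is no stated figure to reproduce. The check compares the texts and adds one proportion.

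**Step 1. Window promised in section 2.10.** Intervention plus follow-up. With treatment over 4 weeks (section 2.8) and the last visit at week 8 (section 2.5), this is weeks 0 to 8, or 8 weeks.

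**Step 2. Window scheduled in Table 1.** The marks in the adverse-event row cover Week 0 and Week 1–4, or 4 weeks.

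**Step 3. Gap.** (8 − 4) / 8 = 4/8 = 50% of the calendar window has no scheduled enquiry. With a Week 8 mark the gap would be (8 − 8) / 8 = 0.

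**Step 4. Is an empty Week 8 cell a convention of the table?**

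| Table 1 row | Week 0 | Week 1–4 | Week 8 |
|---|---|---|---|
| ISI | × | × | × |
| fNIRS | × | × | × |
| PSQI | × | × | × |
| HAMA | × | × | × |
| Overall clinical efficacy | | × | × |
| Adverse events | × | × | |
| Sleep medication use | × | × | × |
| Compliance | × | × | × |

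Seven of the eight outcome and assessment rows are marked at Week 8. The adverse-event row is the only exception. Two rows of its own block show the mark in the same layout, so a fault in reading the table is unlikely.

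**Step 5. Does another section fill the gap?** The vital-sign checks and the observation period after stellate ganglion needling (section 2.10) are tied to treatment sessions and end with them. The 24-hour rule for serious events governs how fast a known event is reported, not when patients are asked. Section 2.9 lists the week-8 assessments without adverse events. No section sets another enquiry after week 4.

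**The case against.** The strongest reply is that section 2.10 is the dedicated safety section and its wording is unambiguous. Staff must record follow-up events, including how long they lasted and how they ended. Serious events carry a reporting duty with no cut-off at week 4, and a clinician sees patients at week 8. On this view the empty cell is a missing mark in a condensed journal table.

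Much of this stands. The documents do not support some stronger conclusions that a reader might draw:

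- *That follow-up events will be lost or found only by accident.* Section 2.10 gives reported events a route into the record. What is missing is the scheduled question.
- *That case report forms will omit the item because they are built from Table 1.* The article describes no forms and does not say how they are derived.
- *That half the safety information is at risk.* The 50% is calendar time. Needling ends at week 4, section 2.10 treats many of the neck-related symptoms as arising during the procedure, and no event type is described as first appearing after week 4.
- *That an upper confidence limit for zero events among the 40 treated patients measures the loss.* That limit depends only on the number of patients and the event count. It is the same for a 4-week and an 8-week window.

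The reply does not remove the inconsistency. A duty to record is not a scheduled enquiry, and the published schedule contradicts the period that the safety section names.

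**Conclusion.** The inconsistency is confirmed. Section 2.10 promises adverse-event recording through week 8, while Table 1 schedules it only through week 4. If the schedule is followed as printed, weeks 5–8 lack systematic enquiry in both arms, and the between-arm safety comparison for that period rests on unprompted reports.

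Severity is modest but above clerical, because answers not sought at week 8 are hard to recover later. The conclusion assumes that the printed table reflects the schedule in use; the full protocol, which is not shown, may already carry the mark. Differential reporting between arms is a plausible risk from the open design, and the documents give nothing from which to quantify it. The efficacy estimates, the alpha allocation and the power calculation are unaffected.

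**What to change.** Reconcile Table 1 with section 2.10 by marking Week 8 in the adverse-event row. At that visit, put the same adverse-event enquiry, in the same words, to patients in both arms, covering the time since week 4 and the status of any event still open then. Because answers about neck symptoms may reveal the arm, ask after the outcome scales are complete or use staff other than the blinded assessor.

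The cost is one table cell and a few minutes at a visit that already takes place. Section 2.12 requires ethics committee approval for changes to the assessment schedule, so the correction may need an amendment. If any patients have already passed week 8 without the enquiry, report their number by arm alongside the safety results.

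### The adverse-event grading in section 2.10 fits the same event into two grades and mixes severity with seriousness; separately, a set observation period is stated for the SG arm only

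*Protocol article*

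**What the plan says.** Section 2.10 (Assessment of safety) defines three grades, largely by example.

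- Mild: "Mild AEs include transient symptoms requiring no specific treatment, such as local pain, minor ecchymosis, or transient dizziness".
- Moderate: "Moderate AEs include symptoms requiring clinical management or observation, such as persistent local pain, moderate hematoma, vasovagal reaction", followed by further examples.
- Severe: "Severe AEs include marked functional impairment, hospitalization, or serious events such as suspected neurovascular injury". The list of examples ends with "expanding cervical hematoma, pneumothorax, or loss of consciousness".

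The management paragraph that follows says: "In cases of dizziness or needle syncope, the procedure will be immediately terminated; the participant will be placed in a supine position". Vital signs and SpO2 are then watched without a break until the participant has recovered. The rule is not limited to persistent dizziness or to one arm.

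The closing paragraph of the section has vital signs taken before and after every treatment, without restriction by arm. It adds that "participants receiving SG acupuncture will be observed for at least 30 min" and gives no counterpart for controls. Serious adverse events go to the ethics committee within 24 hours.

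Section 2.8 gives both groups 12 sessions. Section 2.3 randomizes 40 patients to each arm.

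**The concern.** A grading rule should lead two people with the same facts to the same grade. Here the examples of one grade and the management rule point to different grades for dizziness, and the position of needle syncope is left to the reader. Because the Severe grade is partly defined by hospitalization and serious events, the choice of grade can also influence whether an event is treated as reportable within 24 hours.

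The second issue is detection. A longer required watch in one arm gives more opportunity to see minor events there. The acupuncturists cannot be blinded (section 2.7) and there is no sham SG procedure (acknowledged in the Discussion), so nothing else in the design evens this out. The Introduction presents ultrasound-guided SG acupuncture as potentially safer and more practical than stellate ganglion block, and the adverse-event record is the trial's own evidence on its safety.

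**Working it through.** The plan states no figure to reproduce, so the check is mainly a comparison of text.

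**Step 1. Grades set against the management rule**

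| Event | Grade by listed example | What else the text says | Second grade it fits |
|---|---|---|---|
| Transient dizziness during a session | Mild, no specific treatment needed | Procedure ended, supine position, continuous monitoring until recovery | Moderate, because management or observation is required |
| Needle syncope | None stated | Same management rule | Moderate if read as a vasovagal reaction; Severe if read as loss of consciousness |

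The dizziness row rests on the text alone: the event is a named Mild example, and the required response is observation. No rule says which criterion takes precedence. The conflict is confined to dizziness during a procedure, since the rule ends the procedure; transient dizziness arising later stays Mild without difficulty. The syncope row is an inference from the labels, because section 2.10 does not itself equate needle syncope with either listed term.

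**Step 2. Severity and seriousness**

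The Severe grade joins three kinds of criterion: intensity (marked functional impairment), an outcome (hospitalization), and a class of serious events with examples. The 24-hour report is then tied to serious adverse events. In the text shown, seriousness is used to define a severity grade and also to trigger reporting. A brief faint could be recorded as Moderate by one rater. Another could record it as Severe, under a heading whose examples are called serious.

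**Step 3. Observation by arm**

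Inputs: 12 sessions per participant (section 2.8); 40 participants per arm (section 2.3); at least 30 minutes, SG participants only (section 2.10). Assumptions: the period applies to every session, follows the session, and all planned sessions are given.

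- Sessions with a stated observation period, SG arm: 40 × 12 = 480.
- Sessions with a stated observation period, control arm: 0 of 40 × 12 = 480.
- Stated minimum per SG participant: 12 × 0.5 h = 6 h.

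These figures describe unequal opportunity to detect events. They do not count missed or misgraded events.

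**Step 4. Does routine observation change the grade?**

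The Moderate criterion concerns symptoms that require observation. The 30-minute period applies whether or not there is a symptom. On the natural reading, a minor ecchymosis noticed during it still needs no observation and stays Mild. Only a grader who counted the routine period would move such events up, and that would happen in the SG arm alone. The text does not exclude that reading.

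**The case against.** A reader might infer that adverse-event grades cannot be compared between arms at all. The documents do not support that. One scale applies to everyone, and the dizziness and syncope rule that creates the overlap is not specific to an arm. An ambiguity shared by both arms blurs the grades but does not by itself bias the comparison.

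A reader might also infer that the Moderate grade depends on the SG observation period. As step 4 shows, that uses observation in two senses.

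Controls are not unobserved either. Their needles are retained for 30 minutes, with manipulation and sensation ratings at insertion and at 10 and 20 minutes (section 2.8.1). Vital signs are taken before and after treatment in both arms, and all adverse events are to be recorded. The text does not say when the SG period starts, so overlap with needle retention is not excluded. Unequal detection is therefore possible, but it is not shown.

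On syncope, the list could be read as a hierarchy in which a vasovagal reaction is Moderate unless consciousness is lost. That is a reasonable reading, but the text does not state it. Nor does the text say that every Severe event is serious, so a definite link from grade to 24-hour reporting cannot be claimed.

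Finally, a formal definition of a serious adverse event and the wording of adverse-event questions may well be in the full protocol, and their absence from an article is no fault. The point here concerns what the article does state: hospitalization and serious events used as criteria for a severity grade, and an example that conflicts with the management rule. The data analysis section names no between-arm test of adverse events, which limits the formal consequence. A descriptive comparison by arm would still rest on these grades.

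**Conclusion.** The concern holds in a limited form. The grading text is internally inconsistent for dizziness during a procedure, leaves needle syncope open to two grades, and mixes severity with seriousness. Separately, the stated observation period covers one arm only, which creates a risk of unequal detection.

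Neither problem can be given a size. The documents contain no event rates, and the 480 sessions and 6 hours are exposure to observation rather than error. The conclusion assumes that dizziness in the management paragraph means any dizziness, as written, and that the 30 minutes are additional to the session; if they overlap with needle retention, the detection issue is smaller and the grading issue is unchanged. This should be corrected, but it does not threaten the efficacy analysis.

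**What to change.** 1. Reconcile the grading examples with the management paragraph so that each listed event, including needle syncope, falls in one grade only. Which grade is for the investigators to decide.
2. Record seriousness as a separate yes/no field with its own definition, and tie the 24-hour report to that field rather than to the grade.
3. State that routine observation after a session does not count toward the grade.
4. Ask both arms the same short set of adverse-event questions at the same existing visit points, for example at the end of each session and the start of the next. Base the between-arm comparison on those answers, and report separately any event found only during the SG observation period.

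The cost is protocol and case-report-form wording and a few minutes per session. No change to clinical management is proposed; the observation period and the response to dizziness or syncope are left as the investigators set them.
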